## Methods

### Setting

The required data will be collected from childbirth preparation training courses that are regularly held in Milad Hospital, Tehran, Iran. These courses have high educational quality and are based on a precise schedule, according to the educational plans defined by the Ministry of Health and Medical Education of Iran. Notably, these courses are held in classes that contain 10-12 individuals at the prenatal clinic of Milad Hospital, which is one of the main referral hospitals in Tehran province.

At Milad Hospital, where all participants in the three groups will be selected from, it is mandatory for pregnant women to attend childbirth preparation classes in order to deliver their children at this hospital, so women who wish to give birth in this hospital have to participate regularly in these classes (participating in six sessions from eight at least). The samples in the virtual and in-person intervention groups will be selected among these women. There is another group of women who only visit a specialist or midwife to receive a pregnancy care and advice, and do not want to give birth at Milad Hospital or attend the preparation classes. These people will be used for the control group.

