Despite the rapid development of social media and their ever increasing popularity among members of the society, especially pregnant women, little research has been conducted on the virtualization of childbirth preparation training courses. In a study of teaching exclusive breastfeeding methods through Telegram social media, the mothers stated that Telegram-based education was more useful than in-person participation in the breastfeeding training courses, they also believed that Telegram social media is an effective educational tool in the field of healthcare [11]. It has also been shown that e-learning can increase the level of satisfaction and awareness of primiparous women regarding prenatal care, compared to educational booklets [16]. Although these results are promising, it is not clear whether virtualize interventions will be feasible for childbirth preparation training in Iran.

An investigation of childbirth preparation training courses showed that these courses have had little effect on pregnancy outcomes in the past few years, since the rate of cesarean sections is still high in Iran [3]. This can be attributed to factors, such as the lack of awareness and unwillingness of pregnant women to participate in natural childbirth training courses, overcrowded classes at hospitals, lack of time (especially among employed women), living far away from centers that offer such trainings, and heavy urban traffic jam, especially in densely populated cities such as Tehran.

Although attending childbirth preparation classes seems beneficial for all pregnant women, these classes are not very popular in Iran. Also, none of the studies available on e-learning in the literature has specifically targeted pregnant women, who probably would benefit the most from the lifestyle changes. Due to the importance of childbirth preparation trainings among pregnant women and ease of access to internet and virtual communication devices such as smartphone in Iran, the present study will be conducted to investigate the feasibility and the effect of childbirth preparation training courses using two in-person and virtual education methods on the pregnancy experience, FOC, birth preference, and type of delivery in pregnant women.

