The primary objective of study is the feasibility of recruitment and feasibility of intervention adherence of participants in both in-person and virtual education groups. The secondary objectives are the effect of childbirth preparation training courses using two in-person and virtual education methods on the pregnancy experience, FOC, birth preference, and type of delivery in pregnant women.

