### Measurements and feasibility outcomes

The primary outcome of the present study would be the study feasibility that will be assessed based on recruitment and intervention adherence for all of the participants in both groups.

The secondary outcome of the present study would be the improvement of pregnancy experience measured by the brief version of the pregnancy experience scale (PES) [19]. The secondary outcome would be the decreased FOC measured by the version A of Wijma Delivery expectancy/experience questionnaire (WDEQ-A) [20]. In addition, the other outcomes would be the birth preference and type of delivery, respectively. Data collection is shown in the flow diagram (Fig. 1). Data will be collected at 3 times by self-reporting method through Telegram messages: Recruitment (demographic characteristics questionnaire, PES, WDEQ-A) ≈ 18-20 weeks (T1); 36-38 weeks (PES, WDEQ-A, and birth preference) (T2); the first few days of postpartum (type of delivery) (T3).

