### Analytic plan

Feasibility of recruitment will be achieved if ≥ 30% of eligible participants enroll in the study, and ≥ 80% participants complete follow-up assessments at 36-38 weeks (PES, WDEQ-A, and birth preference) (T2); the first few days of postpartum (type of delivery) (T3). Feasibility of intervention adherence will be achieved if average proportion of intervention adherence rate is ≥ 0.8 (participating in six sessions from eight at least for both the virtual and in-person childbirth preparation training groups).

The collected data will be analyzed in the SPSS software (version 19) using descriptive statistics, such as frequency distribution tables. Also, the Chi-square test and one-way analysis of variance (ANOVA) will be used to compare the quantitative and qualitative variables in three groups, respectively. In addition, the paired *t* test will be employed for intragroup comparison. The *p* value of less than 0.05 will be considered statistically significant.

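### The primary adherence criterion equals the hospital's own attendance minimum for the women in groups A and B, so a pass, especially one averaged over both arms, cannot separate feasibility from required attendance

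*Protocol article*

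**What the plan says.** **Hospital rule and source of the groups (Setting).** Classes are a condition of delivery at the study hospital: "women who wish to give birth in this hospital have to participate regularly in these classes (participating in six sessions from eight at least". Of the two training arms it says: "The samples in the virtual and in-person intervention groups will be selected among these women". The control group comes from women who "do not want to give birth at Milad Hospital or attend the preparation classes".

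**Status of adherence.** The Introduction makes it half of the primary objective: "The primary objective of study is the feasibility of recruitment and feasibility of intervention adherence of participants in both in-person and virtual education groups". The section on measurements and feasibility outcomes says feasibility will be judged on "recruitment and intervention adherence for all of the participants in both groups".

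**Criterion (Analytic plan).** "Feasibility of intervention adherence will be achieved if average proportion of intervention adherence rate is" at least 0.8, with adherence explained as "participating in six sessions from eight at least for both the virtual and in-person childbirth preparation training groups".

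**Exclusions after enrolment.** Inclusion and exclusion criteria removes group A women who give no Telegram feedback and group B women with low attendance. The Intervention section also removes group A women who stay unresponsive after a message and a phone call. The article does not say whether excluded women stay in the adherence denominator.

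**The concern.** The cut-off that defines an adherent participant is the same as the attendance the hospital already demands, and both training arms are recruited only from women subject to that demand. Women who do not want the classes go to the control group, where adherence is not measured.

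A high adherence rate could therefore reflect the course, the condition on place of delivery, or both, and the criterion cannot tell these apart. The Introduction asks whether virtual training is feasible in Iran and lists, among the barriers, "the lack of awareness and unwillingness of pregnant women to participate in natural childbirth training courses". The Discussion intends to use the lessons learned in applying for a large-scale grant. A rate obtained under compulsion may overstate what a later trial would see where attendance is voluntary.

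The wording about an average adds a second risk. If the two arms are combined, the arm bound by the rule can carry the arm whose feasibility is the open question.

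**Working it through.** The plan gives no expected adherence rate, so there is no figure of its own to reproduce. The check compares the two rules and then shows what follows by arithmetic.

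**Inputs from the protocol article**
- Hospital minimum: 6 of 8 sessions (Setting).
- Definition of adherence: at least 6 of 8 sessions, both arms (Analytic plan).
- Target: 0.8 (Analytic plan).
- Women per arm: 55 (Sample size), so 110 in the two training arms.

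**Step 1. Compare the cut-offs.** Both are 6/8 = 0.75 of sessions. What bare compliance with the hospital rule yields depends on how the average proportion is read:
- *Share of women with at least six sessions.* If every woman does exactly what the hospital requires, the share is 1.00, which is above 0.80. The parenthesis in the Analytic plan favours this reading.
- *Mean share of sessions attended.* Six sessions each gives 0.75, which misses 0.80. The target is 0.80 × 8 = 6.4 sessions, so 6.4 − 6 = 0.4 of a session per woman must come beyond the requirement.

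**Step 2. Group A.** The article does not say whether virtual sessions count towards the hospital rule.
- If they do, group A is under the same requirement as group B.
- If they do not, the rule does not compel virtual participation. Group A's rate is then informative about the virtual course, but it is not comparable with group B's.

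**Step 3. Averaging over the arms.** With equal arms and a mean of 0.80, group A needs 2 × 0.80 − pB, where pB is group B's rate.
- pB = 1.00 (assumed): 1.60 − 1.00 = 0.60.
- pB = 0.95 (assumed): 1.60 − 0.95 = 0.65.

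**Step 4. Chance of passing.** Exact binomial with n = 55 women in the arm. Judged alone, the arm needs 0.80 × 55 = 44 adherent women. Averaged with group B fixed at 55 of 55, group A needs 0.80 × 110 − 55 = 33. All true rates are assumed; the article gives none.

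| Assumed true rate in the arm | Judged alone (≥ 44 of 55) | Group A, averaged with group B at 1.00 (≥ 33 of 55) |
|---|---|---|
| 0.60 | 0.001 | 0.56 |
| 0.70 | 0.07 | 0.96 |
| 0.80 | 0.58 | > 0.99 |
| 0.90 | 0.993 | > 0.99 |
| 0.95 | > 0.999 | > 0.99 |

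The first two rows matter most. A virtual arm with true adherence of 0.60 or 0.70 would usually fail alone, but would often or nearly always pass once averaged with a fully compliant group B.

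**Step 5. Denominator.** Suppose, as an example, that 5 of 55 women are excluded for non-response or low attendance and 40 of the rest reach six sessions. Without the excluded women the rate is 40/50 = 0.80, a pass; with them it is 40/55 = 0.73, a fail.

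**The case against.** A reader might infer that a pass would show only obedience to a hospital rule in both arms, or that the criterion cannot fail. The documents do not support either.

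- **Group A may not be compelled.** If virtual sessions do not satisfy the rule, virtual participation is not required by it and does reflect willingness. This stands, so the loss of meaning is certain only for group B and conditional for group A.
- **A rule does not guarantee attendance.** A woman can choose to deliver elsewhere or drop out, and the article plans for low attenders and non-responders. This stands, so a pass is not automatic.
- **Unwillingness is only one of the barriers listed.** The Introduction also names lack of awareness, crowded classes, lack of time, distance and traffic. A rule does not remove crowding, distance, traffic or lack of time, so reaching six sessions despite them is still informative.
- **Bare compliance fails on the mean-sessions reading.** This is true (0.75 against 0.80), but the parenthesis points to the other reading, and the gap is only 0.4 of a session.
- **Pooling is not stated.** Naming both groups could equally mean that each must reach the target. This stands: pooling is one possible reading.
- **The rule is disclosed and is the real local setting.** The rate would be usable for a later trial at the same hospital. That limits the harm but does not make the rate applicable where attendance is voluntary.

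The same cut-off, the restricted source of both arms, and the lack of a clear arm-by-arm test all remain.

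**Conclusion.** The point holds in a limited form and should be fixed. For group B, and for group A if virtual sessions count towards the hospital's condition, meeting the adherence criterion cannot separate feasibility from required attendance. If virtual sessions do not count, the arms' rates measure different things and should not be compared or averaged.

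On the averaged reading, a group B at 1.00 lowers what group A must achieve from 0.80 to 0.60. A virtual arm with true adherence of 0.60 then passes with probability 0.56 instead of 0.001. These figures assume 55 women per arm, the share-of-women reading, pooled arms, full compliance in group B and the stated true rates, none of which the article fixes except the arm size.

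Only the adherence half of the primary outcome is affected. The criteria of at least 30% enrolment and at least 80% follow-up are separate.

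**What to change.** Change the Analytic plan as follows:

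1. Define adherence as the share of all women allocated to an arm with at least six of eight sessions. Women later excluded for non-response or low attendance stay in the denominator.
2. Require at least 0.80, that is 44 of 55, in each arm separately. The conclusion on virtual feasibility rests on the virtual arm's result alone.
3. State whether virtual sessions satisfy the hospital's delivery condition.
4. Limit the adherence conclusion to settings where attendance is mandatory.

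This needs no further participants and no change to the timetable. The downside is that the criterion may be harder to meet and the claim is narrower.

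A hospital waiver of the rule for study participants is not needed. It would require a policy change, and release from a mandatory course could itself draw women into the study and inflate the enrolment criterion.

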### Research design and sampling

This feasibility quasi-experimental study with a control group was reported in accordance with the Consolidation Standards of Reporting Trials (CONSORT) statement for pilot and feasibility trials (Additional file 1) [17]. The current study will be conducted on 165 primiparous women with 18-20 gestational weeks that will be selected by convenience sampling method. The researcher will attend the prenatal clinic for sampling on a daily basis. The participants will be equally allocated into two studies and one control groups (Fig. 1). The participants in study groups A and B will receive virtual and in-person childbirth preparation trainings, respectively. Also, the control group will receive no education on childbirth preparation during pregnancy.

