The teaching instructors for the training sessions will be midwives who are certified as childbirth educators. If needed, they will use textbooks, video and audio files, music, posters, medical moulages, whiteboard, and slides. Table 1 presents the content, time, and objectives of the educational sessions that are similar for both study groups. To increase the generalizability of the results, another group will be considered as the control group that receives no education about pregnancy and childbirth preparation. It is important to note that all three groups will receive the routine prenatal care provided at the hospital. All participants will also be followed up until delivery.

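### Controls are women who want neither the classes nor a birth at Milad Hospital, so training-versus-control contrasts are confounded with intended place of birth and prior attitude, yet are planned as unadjusted effect tests

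*Protocol article*

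**What the plan says.** The protocol article, under Setting, describes two kinds of women at the clinic. Those who wish to deliver at Milad Hospital must attend at least six of eight classes, and of them it says: "The samples in the virtual and in-person intervention groups will be selected among these women". The others come only for prenatal care and "do not want to give birth at Milad Hospital or attend the preparation classes. These people will be used for the control group".

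Research design and sampling calls the work "This feasibility quasi-experimental study with a control group". It recruits 165 women "that will be selected by convenience sampling method" and then says: "The participants will be equally allocated into two studies and one control groups". The text names no allocation method, and the figure it points to is not available to us.

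The Introduction makes feasibility the primary objective and adds: "The secondary objectives are the effect of childbirth preparation training courses using two in-person and virtual education methods", on pregnancy experience, fear of childbirth, birth preference and type of delivery. Sample size rests the 55 per group on a cesarean rate falling from 0.55 to 0.30 relative to control. Under Analytic plan, "the Chi-square test and one-way analysis of variance (ANOVA) will be used to compare" the three groups, with a 0.05 threshold and no adjustment named. The reason given for the control arm, under Intervention, is: "To increase the generalizability of the results, another group will be considered as the control group".

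**The concern.** Before any teaching starts, trained and control women already differ in two respects that define their group: where they intend to give birth, and whether they want the classes. Both can bear on birth preference and type of delivery. The Introduction itself counts unwillingness to attend among the reasons why the courses have had little effect on a high cesarean rate, which links the trait that defines the controls to an outcome.

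If the plan is followed as written, a difference in cesarean rate between trained and control women would be read as an effect of training when it could come from hospital practice or prior intention. The same mechanism could run the other way and hide a real benefit. The Discussion expects more vaginal deliveries and less fear as main results and sees the study as groundwork for a large grant application, so a misread contrast could carry forward.

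**Working it through.** **1. How group relates to its determinants**

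| | Groups A (virtual) and B (in-person) | Control |
|---|---|---|
| Intended place of birth | Milad | not Milad |
| Classes | required for the intended birth | not wanted |
| Source | one pool | a different pool |

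No control woman intends a Milad birth, and no trained woman is drawn from those who intend another hospital. A regression with intended hospital as covariate therefore has no data from which to separate hospital from training. This applies to type of delivery and, so far as preference follows the choice of hospital, to birth preference.

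It does not apply in the same way to PES and WDEQ-A. Measurements and feasibility outcomes places these at 18-20 weeks (T1) and 36-38 weeks (T2), before delivery. Hospital delivery practice does not determine them, and a baseline value is available. What remains for them is self-selection.

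**2. The plan's own sample-size figure**

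The printed cesarean equation, with its own rounded inputs, is

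[1.96 × √(2 × 0.42 × 0.57) + 0.84 × √(0.55 × 0.45 + 0.3 × 0.7)]² / 0.25² = 59.3,

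not the stated 50. That is a separate matter and this point does not depend on it. What matters here is that the calculation is built on the contrast with control. I keep 50 analysed per group below because it is the plan's figure.

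**3. How often the planned test would reject with no training effect**

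Inputs: control cesarean rate 0.55 (Sample size); 50 per group (Sample size); two-sided 0.05 (Sample size uses 1.96). The underlying rate among Milad women, m, is not in the documents and is an assumption, shown over a range. Chi-square is taken as the test for type of delivery.

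Three-group chi-square, 2 degrees of freedom, critical value 5.99, with A and B both at m:

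- overall mean = (2m + 0.55)/3
- noncentrality = 50 × [2(m − mean)² + (0.55 − mean)²] / [mean × (1 − mean)]

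Example, m = 0.40: mean = 0.45; noncentrality = 50 × (2 × 0.05² + 0.10²) / (0.45 × 0.55) = 50 × 0.015 / 0.2475 = 3.03; rejection about 32%.

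Pairwise z-test of one trained group against control, with gap d = 0.55 − m: rejection = Φ[(d − 1.96·se0)/se1] + Φ[(−d − 1.96·se0)/se1], where se0 uses the pooled rate and se1 the separate rates. Example, m = 0.40: se0 = 0.0999, se1 = 0.0987, giving (0.15 − 0.1958)/0.0987 = −0.46, so about 32%.

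| Assumed Milad rate m | Three-group chi-square | One trained group vs control |
|---|---|---|
| 0.55 | 5% | 5% |
| 0.50 | 7% | 8% |
| 0.45 | 16% | 17% |
| 0.40 | 32% | 32% |
| 0.35 | 55% | 52% |

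The three-group column comes from exact enumeration of the binomial outcomes. The noncentral approximation agrees within about one percentage point.

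The direction is open. At m = 0.65 the mean is 0.6167, the noncentrality is about 1.41 and rejection is about 17%, now with training looking harmful.

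**4. Virtual versus in-person**

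A and B come from one pool, so this contrast does not carry the hospital problem. It compares formats, not training with none, and Intervention also gives group A two in-person sessions. For an assumed 0.40 versus 0.30 at 50 per group, se0 = 0.0954 and se1 = 0.0949, so power = Φ[(0.10 − 1.96 × 0.0954)/0.0949] = Φ(−0.92), about 18%. The 95% interval for the difference would be about ±1.96 × 0.0949 = ±0.19.

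**The case against.** The strongest reply is that the study declares itself a quasi-experimental feasibility study, that recruitment and adherence are primary with their own thresholds (30%, 80% and 0.8), and that effects are secondary. Because classes are compulsory for a Milad birth, an untrained Milad control group cannot be had. All of this stands and limits the seriousness of the point. It does not remove it: the label does not tell a reader that group is tied to intended hospital, and the secondary objectives are still worded as effects, tested at 0.05 and used to set the sample size.

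A full analysis plan might name covariates. For PES and WDEQ-A that would help. For type of delivery it would not, because there is no overlap to adjust over.

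A reader might infer more than the text supports:

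- That A and B are stated to be allocated by convenience. Convenience describes how the 165 women are selected. The allocation method is not stated, although the quasi-experimental label makes randomisation unlikely.
- That no adjustment can help any outcome. The no-overlap argument covers type of delivery and part of birth preference only.
- That controls refuse the classes, or that trained women all deliver at Milad. The text speaks of what women want at recruitment. Actual place of birth is not reported.
- That Milad's cesarean rate is below 0.55. Nothing in the document says so.

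**Conclusion.** The concern holds in this form. Training versus control is confounded with intended place of birth and prior attitude. For type of delivery, and in part birth preference, analysis cannot undo this. For PES and WDEQ-A, self-selection remains but a baseline is available. Testing these contrasts unadjusted as effects can credit training with differences that it did not cause, or hide a benefit.

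The size depends on the unknown Milad rate. Underlying gaps of 5 to 20 points would raise the planned test's rejection rate from 5% to between about 7% and 55% with no training effect. That range rests on assumed rates, 50 analysed women per group and a control rate equal to the national figure.

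Generalizability is not a benefit that this control arm can give, since it comes from outside the class-attending population. The recruitment and adherence objectives are largely untouched, so the point should be corrected but does not threaten the primary aim.

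**What to change.** 1. Treat contrasts with control on type of delivery and birth preference as descriptive, with no effect claim. Record planned and actual place of birth and report type of delivery by place.
2. Compare PES and WDEQ-A at T2 with adjustment for the T1 value (analysis of covariance), and state self-selection as a limitation.
3. Replace the generalizability rationale under Intervention with a plain account of what the control arm can show: the course of these outcomes in women receiving routine care who did not seek the classes.
4. State how A and B are allocated and, since they share one pool, allocate them by a concealed random list. Say that this compares formats, not training with none, and that it is imprecise for cesarean at this size.

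The cost is an amendment, a random list and one or two extra data items, with no extra visits or sessions. The downsides are a weaker cesarean claim, some refusals by women who want one format, and possible contamination between formats within one clinic. Adequate power for A versus B on cesarean would need more women. This fix does not ask for that.
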